## Abstract

**Background:**

Individuals with multiple relatives with colorectal cancer (CRC) and/or a relative with early-onset CRC have an increased risk of developing CRC. They are eligible for preventive measures, such as surveillance by regular colonoscopy and/or genetic counselling. Currently, most at-risk individuals do not follow the indicated follow-up policy. In a new guideline on familial and hereditary CRC, clinicians have new tasks in calculating, interpreting, and communicating familial CRC risk. This will lead to better recognition of individuals at an increased familial CRC risk, enabling them to take effective preventive measures. This trial compares two implementation strategies (a common versus an intensive implementation strategy), focussing on clinicians' risk calculation, interpretation, and communication, as well as patients' uptake of the indicated follow-up policy.

**Methods:**

A clustered randomized controlled trial including an effect, process, and cost evaluation will be conducted in eighteen hospitals. Nine hospitals in the control group will receive the common implementation strategy (*i.e*., dissemination of the guideline). In the intervention group, an intensive implementation strategy will be introduced. Clinicians will receive education and tools for risk calculation, interpretation, and communication. Patients will also receive these tools, in addition to patient decision aids. The effect evaluation includes assessment of the number of patients for whom risk calculation, interpretation, and communication is performed correctly, and the number of patients following the indicated follow-up policy. The actual exposure to the implementation strategies and users' experiences will be assessed in the process evaluation. In a cost evaluation, the costs of the implementation strategies will be determined.

**Discussion:**

The results of this study will help determine the most effective method as well as the costs of improving the recognition of individuals at an increased familial CRC risk. It will provide insight into the experiences of both patients and clinicians with these strategies.

The knowledge gathered in this study can be used to improve the recognition of familial and hereditary CRC at both the national and international level, and will serve as an example to improve care for patients and their relatives worldwide. Our results may also be useful in improving healthcare in other diseases.

**Trial registration:**

ClinicalTrials.gov NCT00929097

## Background

The lifetime risk of developing colorectal cancer (CRC) in Western society is 5 to 6%[1,2]. Familial and hereditary cancers account for approximately 15 to 20% of all CRCs [3-5]. In these families, healthy relatives of CRC patients may have an increased risk of developing CRC themselves. This so-called familial CRC risk can be divided into three groups, based on cumulative lifetime risks of developing CRC:

1. Average: familial CRC risk below 10%.

2. Moderate: familial CRC risk of 10-15%.

3. High: familial CRC risk above 15%.

For each group, a different follow-up policy applies. For individuals with an average familial CRC risk, neither surveillance nor genetic counselling is indicated. For individuals with a moderate familial CRC risk, surveillance by regular colonoscopy is indicated. For individuals with a high familial CRC risk, referral for genetic counselling is recommended. Identification of individuals with an increased familial CRC risk is crucial because surveillance significantly reduces CRC-related morbidity and mortality, by 43 to 80% and 65 to 81%, respectively[6,7]. Both underuse and overuse of surveillance and genetic counselling have a significant impact on patients and their relatives, and may lead to unnecessary costs.

Familial CRC risk is assessed by family history and, in a subset of patients, microsatellite instability (MSI) analysis performed by pathologists. Unfortunately, both procedures are difficult. Previous research has shown that patient family history often is missing or incomplete, and information provided by patients is not always accurate[4,8-11]. Furthermore, interpretation of the family history (determining the indicated follow-up policy) is not always correct[12]. Pathologists' selection of patients for MSI is often incomplete, while clinicians regularly interpret the results incorrectly [Overbeek LI, Hermens RP, van Krieken JH, Adang E, Casparie M, Akkermans R, Nagengast FM, Ligtenberg MJ, Hoogerbrugge N. A tailored implementation strategy increases involvement of pathologists in the recognition of patients at risk for Lynch syndrome: cluster randomised controlled trial, submitted] Consequently, only 12 to 30% of CRC patients with a high familial CRC risk are referred for genetic counselling[4,10,13-15]. Other studies have shown that many CRC patients referred to a familial cancer clinic belong to an average or moderate risk population for whom genetic counselling is not indicated[16,17].

Clinicians involved in the care for CRC patients recognize the need for improvement in this area. Therefore, a multidisciplinary evidence-based guideline on familial and hereditary colorectal cancer (FHCC) was launched in the Netherlands in 2008[18]. An important addition compared to previous national and international guidelines is that surgeons and gastroenterologists (referred to as 'clinicians' in this protocol) have new tasks in calculating, interpretating, and communicating familial CRC risk. Because clinicians are often unfamiliar with these tasks, implementation strategies are needed to ensure that patients and their relatives receive proper counselling and follow-up[14]. In a previous trial, an electronic reminder system specifically aimed at pathologists improved completeness of patient selection for MSI testing [Overbeek LI, Hermens RP, van Krieken JH, Adang E, Casparie M, Akkermans R, Nagengast FM, Ligtenberg MJ, Hoogerbrugge N. A tailored implementation strategy increases involvement of pathologists in the recognition of patients at risk for Lynch syndrome: cluster randomised controlled trial, submitted] In this trial, we will provide support at both clinician and patient level to further implement the guideline.

This trial compares two implementation strategies: a common strategy (*i.e*., dissemination of the guideline) versus an intensive implementation strategy, focussing on clinicians' risk calculation, interpretation, and communication, as well as patients' uptake of the indicated follow-up policy.

An effect, process, and cost evaluation will be performed. The improvement of the identification and referral of patients at an increased familial CRC risk will lead to a higher number of individuals following an appropriate surveillance program, thereby reducing CRC-related morbidity and mortality.

## Methods

### Study design and setting

A clustered randomized controlled trial including an effect, process, and cost evaluation will be conducted in eighteen community hospitals. All patients with CRC diagnosed under the age of 70 years and their clinicians will be invited to participate. To prevent contamination bias, randomization will take place at hospital level. Stratification will take place according to hospital size (<500, 500 to 700, and >700 beds), and be performed by means of a computerized randomization system. This study was approved by the Committee on Research Involving Human Subjects of the region Arnhem-Nijmegen.

### Primary objectives

This trial compares two implementation strategies: a common strategy versus an intensive implementation strategy, focussing on clinicians' risk calculation, interpretation, and communication, as well as patients' uptake of the indicated follow-up policy.

### Hypothesis

Providing patients and clinicians with information on CRC, a risk assessment tool, risk communication aids, and decision aids will improve calculation, interpretation, and communication of the familial CRC risk by clinicians, as well as patients' uptake of the indicated follow-up policy more than dissemination of the guideline only.

### Outcome measures

#### Effect evaluation

1. The percentage of CRC patients for whom a correct familial CRC risk is calculated by clinicians.

2. The percentage of CRC patients for whom a calculated familial CRC risk is correctly interpreted by clinicians.

3. The percentage of CRC patients with whom a calculated familial CRC risk and/or follow-up policy is communicated by clinicians.

4. Patients' uptake of the indicated follow-up policy.

#### Process evaluation

1. Actual exposure to the different elements of the implementation strategies.

2. The experiences of patients and clinicians with these elements.

#### Cost evaluation

Costs of the implementation strategies in relation to the number of correctly referred patients.

#### Participants

Clinicians from eighteen hospitals will participate. All their patients diagnosed with CRC under the age of 70 years during the six-month inclusion period are eligible for inclusion. Patients must be able to provide informed consent and be able to read and understand Dutch. Patients previously referred for genetic counselling for CRC are excluded. Patients will be selected by PALGA (Pathologisch-Anatomisch Landelijk Geautomatiseerd Archief), the nationwide network and registry of histo- and cytopathology in the Netherlands[19].

All patients will receive a patient information letter, signed by their treating clinician, along with an informed consent form. After signing the informed consent form, they will be included in the study.

### Interventions

#### Implementation strategies in both groups

In both the control group and the intervention group, clinicians will receive the FHCC guideline.

#### Intensive implementation strategy in the intervention group

The intensive implementation strategy is summarized in Figure 1 and consists of the following implementation tools: a website for patients and clinicians; education for clinicians; and a risk communication tool for clinicians.

**Figure 1 F1:**
[figure not shown]
**Intensive implementation strategy for the intervention group, aimed at both patients and clinicians**. The rhombuses in this figure represent the tasks clinicians have in calculation, interpretation and communication of the familial colorectal cancer (CRC) risk in CRC patients. It also shows the various elements of the intensive implementation strategy aimed at both patients and clinicians (in yellow and green, respectively) that will be compared to dissemination of the guideline on familial and hereditary colorectal cancer only. Familial CRC risk: cumulative lifetime risk of developing CRC for first-degree relatives of CRC patients.

#### Website

The website consists of the following items:

1. A summary of evidence-based and relevant information about familial CRC risk (lifetime risk of developing CRC). Natural frequencies with the same denominator and visual displays will be used. Absolute risks will be presented, as well as in comparison to the population risk. The outcomes are offered in both positive and negative frames (*e.g*., the risk of developing CRC as well as the chance of not developing CRC). The focus is on familial CRC risk and the different follow-up policies. The information is presented in two different formats, one for patients and one for clinicians.

2. A risk assessment tool to calculate patients' familial CRC risk. Patients fill in medical information about themselves and their relatives with regard to CRC and other cancers. Clinicians can use the tool as well. The calculated familial CRC risk is given in the same format as the rest of the website. Advice for follow-up is offered based on this risk, as well as a reminder to use the corresponding decision aid, if applicable.

3. Decision aids, aimed at facilitating decisions involving the uptake of the indicated follow-up policy (one for surveillance and one for genetic counselling). Tools supporting patients in making informed choices about their healthcare, such as decision aids, have been shown to improve knowledge, clarify preferences, and reduce uncertainty around decision making, with high levels of acceptability among consumers[20,21]. The decision aids used in this trial provide balanced information on different options, *i.e*., to be referred for surveillance/genetic counselling or not. The following items are addressed: background information, benefits and harms, and the potential impact on the patient and their relatives. Worksheets are provided for patients to list and rate the importance of the benefits and harms for themselves.

The website is available exclusively to patients and clinicians in the intervention group. A login name and password will be provided upon inclusion. Patients can use the website independently before or after regular follow-up visits, and are encouraged to discuss the results with their clinician. They are instructed to keep the decision aid within their family, and not share it for reasons of research integrity. To minimize contamination bias, after the trial all patients in the control group will be asked if they were exposed to the website.

#### Education

In an educational meeting, clinicians in the intervention group will be trained to use the FHCC guideline.

#### Risk communication tool

Clinicians will receive a tool for communicating the familial CRC risk with their patients during a regular follow-up visit. The tool consists of written information and visual displays of the population risk of CRC, an explanation of the risk level of the patient and his/her relatives, as well as the indicated follow-up policy. It is designed in the same format as the website.

#### Development of the implementation tools

During development, the content and presentation of the website and the risk communication tool will be reviewed by physicians not specifically trained in genetics, and by non-medical personnel as well as representatives from the Dutch CRC patient associations (Vereniging HNPCC-Lynch and Stichting Doorgang). Improvements will be made based on their comments. Before use, the tools will be tested among approximately 20 patients and 20 clinicians. The purpose of this pilot is determining whether the website and the tools are acceptable, the information is presented clearly, and the completion of the tools is feasible.

#### Power calculation

To detect a difference of 20% between the intervention group and the control group in uptake of surveillance by colonoscopy in patients at moderate familial CRC risk, and referral for genetic counselling in patients at a high familial CRC risk, at least 186 patients are required (alpha = 0.05, a two-sided testing and power = 0.80). However, considering an intracluster-correlation coefficient of 0.15 and an average of five patients per clinician, at least sixty clinicians and 300 patients are needed. For eighteen hospitals this means three to four clinicians and 15 to 20 patients per hospital.

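### The sample size is derived for moderate- and high-risk patients but carried to a per-hospital number with no step for the at-risk share of the patients enrolled

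*Protocol article*

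**What the plan says.** The Power calculation section of the protocol article aims at a 20% difference between the arms. The outcome is colonoscopy uptake for those at moderate risk and counselling referral for those at high risk. The unadjusted sample size is tied to these two groups: "referral for genetic counselling in patients at a high familial CRC risk, at least 186 patients are required". Testing is two-sided at 5% with 80% power. With an intracluster correlation of 0.15 and five patients per clinician this becomes at least 60 clinicians and 300 patients. The section closes: "For eighteen hospitals this means three to four clinicians and 15 to 20 patients per hospital".

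The Participants section defines who enters: "All their patients diagnosed with CRC under the age of 70 years during the six-month inclusion period are eligible for inclusion". Study design and setting says the same, and neither section has a familial-risk criterion. Under Data collection, Effect evaluation, the formal risk is worked out from the family-history questionnaire that included patients complete, so risk group is known only after inclusion.

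The Background states that average-risk individuals have no indication for surveillance or counselling. It also gives the only figure in the article that bears on the risk mix: "Familial and hereditary cancers account for approximately 15 to 20% of all CRCs".

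**The concern.** The 186 is a number of moderate- and high-risk patients. Average-risk patients have no indicated follow-up to take up, so they add nothing to this comparison. Yet eligibility takes in patients of every risk level, and the only inflation between 186 and the per-hospital figure is the one for clustering. The reader cannot tell whether 300 and 15 to 20 per hospital count patients at increased risk or all patients enrolled.

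At stake is the only power statement in the article. On one reading, the comparison it describes falls well short of 80% power. On the other, the power statement can stand, but the enrolment it requires is several times 300 and appears nowhere.

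**Working it through.** **Inputs from the article.** Two-sided alpha 0.05, power 0.80, difference 20 percentage points, ICC 0.15, five patients per clinician, 18 hospitals with nine per arm.

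**Assumptions.**
- *Control rate.* None is stated with the power calculation. I use 30% vs 50%, which reproduces 186 (50% vs 70% does too). The 30% is also the upper end of the 12 to 30% referral range in the Background.
- *At-risk share.* The moderate-plus-high share of enrolled patients is not stated. I use 15-20% as a proxy from the Background, and 30-40% to show the range.

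**Step 1: reproduce the plan.** Pooled-variance formula, no continuity correction, equal arms:

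n per arm = [1.96·√(2·0.4·0.6) + 0.8416·√(0.3·0.7 + 0.5·0.5)]² / 0.2² = 93.0, so 186 in total.

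Design effect = 1 + (5 − 1)·0.15 = 1.6, and 186 × 1.6 = 297.6, stated as 300. Then 300/5 = 60 clinicians, 300/18 = 16.7 patients and 60/18 = 3.3 clinicians per hospital. Every printed figure reproduces, and no factor for the risk mix appears.

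**Step 2: suppose 300 counts enrolled patients.** At-risk number = 300 × share. With n = half of that per arm and no clustering, power = Φ{[0.2·√n − 1.96·√(2·0.4·0.6)] / √(0.3·0.7 + 0.5·0.5)}.

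| Assumed at-risk share | At-risk patients | Power, no clustering |
|---|---|---|
| 15% | 45 | 27% |
| 20% | 60 | 35% |
| 30% | 90 | 49% |
| 40% | 120 | 61% |

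Leaving out clustering favours the plan. At 15-20% it makes little difference at clinician level, because five patients per clinician then include only 0.75 to 1 at increased risk. At 30-40% there are 1.5 to 2 per clinician, the design effect is 1 + 0.5·0.15 = 1.075 to 1 + 1·0.15 = 1.15, and power falls to 46-55%.

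At these rates 80% power needs 186 at-risk patients even without clustering. Among 300 enrolled that is a share of 186/300 = 62%, so no minority share is enough.

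**Step 3: suppose 300 counts at-risk patients.** Enrolment needed = 300 / share.

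| Assumed at-risk share | Enrolled in total | Per hospital (÷ 18) | Per clinician (÷ 60) |
|---|---|---|---|
| 15% | 2,000 | 111 | 33 |
| 20% | 1,500 | 83 | 25 |
| 30% | 1,000 | 56 | 17 |
| 40% | 750 | 42 | 12.5 |

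These patients would have to come from the six-month inclusion period. None of these numbers is in the article.

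**Step 4: sensitivity to the control rate.** At the lower end of the Background's range, 12% vs 32%, unclustered power is 36-46% for 45-60 patients and 63-76% for 90-120. The shortfall is smaller but remains. These rates would not have produced 186, however: the same formula gives 134.

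**The case against.** The strongest defence is that 300 already means patients at increased risk. The sentence in the Power calculation supports this grammatically, both sample sizes are given as minima, and all eligible patients over six months are invited with no cap. Enrolment is then set by the inclusion period and the 80% may be met. This reading is open and I do not rule it out. It does not settle the matter, because the plan then relies on an enrolment several times 300 that is not stated.

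Three stronger conclusions are tempting, and the article does not support them.
- *The trial will have only a few dozen relevant patients.* That requires recruitment to stop at 300 and the 15-20% share to apply. The article sets no stopping point. The 15-20% describes all CRCs, not patients under 70 who have not already been referred for genetic counselling, and the effect of those restrictions on the mix is unknown.
- *The trial cannot answer its main question.* The article lists four effect measures without ranking them. Correct calculation, interpretation and communication draw on patients of every risk level, and the definition of correctly referred patients includes those at average risk. Only the uptake and referral comparison is affected.
- *The arithmetic is wrong.* It reproduces throughout. The fault lies in the population to which the result is applied.

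It can also be said that a journal article condenses a fuller protocol, where a recruitment projection may be found. That is fair as to the projection. But the article itself prints the whole chain from effect size to patients per hospital, and that chain does not say whom it counts.

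**Conclusion.** The point holds, conditional on the reading. The Power calculation and the eligibility rule refer to different populations, and nothing in the article connects them.

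If 300 and 15 to 20 per hospital count enrolled patients, the stated 80% is not delivered for the comparison it describes: the unclustered figure is about 27-35% at a 15-20% at-risk share and 49-61% at 30-40%. If they count at-risk patients, the required enrolment is missing: about 1,500-2,000 or 750-1,000 at the same shares. The sizes rest on 30% vs 50% and on assumed at-risk shares. The need to reconcile the sections rests on neither.

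**What to change.** In the Power calculation, state whether 186, 300 and 15 to 20 per hospital count moderate- and high-risk patients or all patients enrolled.

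Take the at-risk share from the baseline assessment, which already collects family history in the same way. Multiply it by the number of eligible patients expected from the 18 hospitals in six months, and report the resulting number of moderate- and high-risk patients with the power for a 20-point difference, or the difference detectable at 80% power.

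The cost is some rewriting and probably a less favourable power statement. Correcting the text requires no extra patients and no change to eligibility.

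### The sample size allows for clustering by clinician only, although hospitals are randomised, so the design does not support the stated 80% power

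*Protocol article*

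**What the plan says.** Under Study design and setting the unit of allocation is explicit: "To prevent contamination bias, randomization will take place at hospital level". The Abstract puts nine of the eighteen hospitals in the control group.

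The Power calculation section starts from an individually randomised comparison. The target is given as "To detect a difference of 20% between the intervention group and the control group", for which "at least 186 patients are required (alpha = 0.05, a two-sided testing and power = 0.80". The control rate is not given. The section then adjusts for clustering: "considering an intracluster-correlation coefficient of 0.15 and an average of five patients per clinician, at least sixty clinicians and 300 patients are needed". Hospitals appear only in the last sentence, as a division of that total: "For eighteen hospitals this means three to four clinicians and 15 to 20 patients per hospital".

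The Data analysis section plans a multilevel analysis with patient, clinician and hospital characteristics. It does not say which levels carry random effects.

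**The concern.** In a cluster randomised trial, the variance of the arm comparison is driven by the unit that was randomised. Here that is a hospital with about 17 patients, not a clinician with five. If patients of different clinicians in one hospital have more similar outcomes than patients of different hospitals in the same arm, that similarity inflates the variance as well. The calculation has no term for it, so it is implicitly zero.

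The protocol itself gives reason to doubt zero. It randomises hospitals to avoid contamination, stratifies by hospital size, records teaching status and the presence of a genetic counselling outpatient department, and plans to correct for case-mix differences between hospitals. The powered outcomes are uptake of colonoscopy and referral for genetic counselling, which local arrangements could plausibly influence.

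The stake is how a null result is read. It could be taken as evidence that the intensive strategy does not work, on the strength of a power figure that the design may not have.

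**Working it through.** **Inputs from the protocol.** Two-sided alpha 0.05; power 0.80; difference 20%, taken as percentage points; ICC 0.15 with five patients per clinician; 60 clinicians; 300 patients; 18 hospitals, so 300/18 = 16.67 patients and 60/18 = 3.33 clinicians per hospital.

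**Assumptions.** (a) Rates of 30% versus 50%. The Background section reports that "only 12 to 30% of CRC patients with a high familial CRC risk are referred for genetic counselling", so 30% is the top of that range, but the protocol does not link it to the calculation. It is used because it reproduces 186 (50% versus 70% does too, with the same variances). (b) A same-hospital, different-clinician correlation ρ_h between 0 and 0.15. The protocol gives no value.

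**Step 1: reproduce 186.** Pooled two-proportion formula, per arm:

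n = [1.96·√(2 × 0.4 × 0.6) + 0.8416·√(0.3 × 0.7 + 0.5 × 0.5)]² / 0.20² = [1.3579 + 0.5708]² / 0.04 ≈ 93, so 186 in total.

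**Step 2: reproduce 300.** Clinician design effect = 1 + (5 − 1) × 0.15 = 1.6, and 186 × 1.6 = 297.6. This is rounded to 300 = 60 × 5. Clinician-level inflation accounts for the stated number, leaving no room for a hospital term.

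**Step 3: add the hospital level.** With ρ_c = 0.15 within clinician,

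DE = 1 + (5 − 1)·ρ_c + (16.67 − 5)·ρ_h = 1.6 + 11.67·ρ_h.

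Effective N = 300/DE. With n = effective N/2 per arm,

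power = Φ{[0.20 − 1.96·√(0.48/n)] / √(0.46/n)}.

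Example at ρ_h = 0.05: DE = 2.183, effective N = 137.4, n = 68.7, and (0.20 − 1.96 × 0.0836)/0.0818 = 0.44, so power is 67%.

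| ρ_h | DE | Effective N | Power (normal) | Power (t, 16 df) |
|---|---|---|---|---|
| 0 | 1.600 | 187.5 | 80.3% | 76.4% |
| 0.01 | 1.717 | 174.8 | 77.5% | 73.5% |
| 0.02 | 1.833 | 163.6 | 74.7% | 70.7% |
| 0.05 | 2.183 | 137.4 | 67.1% | 63.2% |
| 0.10 | 2.767 | 108.4 | 56.7% | 53.2% |
| 0.15 | 3.350 | 89.6 | 48.8% | 45.8% |

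The last column uses a noncentral t with 18 − 2 = 16 degrees of freedom and the unpooled variance. It is a sensitivity result, since the protocol names no reference distribution. The last row equals a single-level hospital calculation at ICC 0.15: 1 + 15.67 × 0.15 = 3.35.

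**Step 4: what limits power.** With 18 hospitals, effective N cannot exceed 18/ρ_h however many patients are added. The ceiling is 180 at ρ_h = 0.10 and 120 at 0.15, both below 186. At those values the number of hospitals is the constraint.

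**Step 5: vary the control rate.** Normal-approximation power for 300 patients:

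| Rates | Unclustered N | ρ_h = 0 | 0.02 | 0.05 | 0.10 | 0.15 |
|---|---|---|---|---|---|---|
| 12% vs 32% | 134 | 91.7% | 87.7% | 81.5% | 71.6% | 63.1% |
| 20% vs 40% | 164 | 85.4% | 80.3% | 73.0% | 62.6% | 54.3% |
| 30% vs 50% | 186 | 80.3% | 74.7% | 67.1% | 56.7% | 48.8% |

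Lower control rates give more power, but they do not reproduce 186.

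**The case against.** Four points can be made for the plan.

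**The arithmetic is right.** Both 186 and 300 reproduce. That stands: the fault is an omitted variance component, not a slip in calculation.

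**The size depends on an unseen parameter.** A reader might infer that the trial really has 49% power and needs about 624 patients (186 × 3.35). The protocol does not support that. It attaches 0.15 to patients of one clinician. Moving it to the hospital assumes that patients of different clinicians are as alike as patients of the same clinician, which is the extreme of the range considered. At ρ_h of 0.01 to 0.02 the loss is only about 3 to 6 points. Lower control rates would soften it further, and stratification by hospital size and hospital covariates may reduce the residual between-hospital variance. All of this limits the size of the shortfall. None of it supplies the missing term, and the calculation takes no credit for covariates.

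**A multilevel analysis is planned.** A reader might infer that standard errors will be too small because clustering will be handled by clinician only. The protocol does not say so: the model includes hospital characteristics, and the list of random effects may properly sit in an analysis plan that is not shown. That worry is therefore only conditional. Equally, a correct hospital-level analysis does not repair the sample size. It would carry the larger variance that the calculation left out.

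**Sharing an allocation is not a source of correlation.** This is correct. The ICC is a within-arm quantity, so the case rests on hospital-level influences on outcome and not on patients being in the same arm.

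**Conclusion.** The point holds. The level of clustering in the power calculation does not match the level of randomisation, and nothing elsewhere in the protocol supplies a hospital-level term. The stated 80% is met under the rates that reproduce 186 only if patients of different clinicians in one hospital are uncorrelated, and even then it is about 76% when allowance is made for 18 units.

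The direction of the error is certain: any positive hospital-level correlation lowers power below what the calculation implies. Its size is not known. Under 30% versus 50% and 0.15 within clinician, power falls from 77.5% to 57% as ρ_h goes from 0.01 to 0.10, with 49% as the extreme case at 0.15. These figures rest on an inferred control rate and an assumed range for ρ_h, and should be reported as a range and not as one corrected value.

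**What to change.** Rewrite the Power calculation paragraph to:

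- state the control rate behind the 186;
- use DE = 1 + (5 − 1)·ρ_clinician + (16.7 − 5)·ρ_hospital;
- report power, or the detectable difference, for 300 patients in 18 hospitals over a stated range of ρ_hospital (for example 0.01 to 0.15), with a small-cluster version on about 16 degrees of freedom alongside.

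Confirm that the multilevel model in the Data analysis section has hospital as a random level, with small-cluster inference for the arm effect. If the analysis plan already says this, a cross-reference is enough.

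The cost is one paragraph and, if needed, one line of model specification. No extra patients are requested. The downside is a less favourable stated power.
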